## Material and methods

### Type of study and location of research

This randomized, controlled, double-blind, parallel, two arm clinical trial will be conducted at the Instituto de Medicina Tropical and of Universidade Federal do Rio Grande do Norte, referred from the ambulatory of infectology of Hospital Giselda Trigueiro (Rio Grande do Norte, Brazil) will be recruited.

Sample size will be determined using maximal inspiratory pressure (MIP) (GPower Software version 3.1.9.2, Kiel, Germany) after a pilot study with five patients in each group (total of 10 patients). Mean and standard deviation will be used to estimate effect size, and a bilateral distribution with alpha error of 0.05 and 80% power will be adopted. Sample size will be adjusted assuming a dropout rate of 20%.

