### Exclusion criteria

Patients with conditions impairing assessments, health complications that justify interrupting data collection (e.g., syncope, intense chest pain, or cough with blood-tinged sputum), hospitalized due to exacerbation of clinical conditions, or requested to leave the study will be excluded.

Regarding recruitment, researchers will contact the Hospital Giselda Trigueiro and inform patients about the study.

The sample will be randomized (www.randomization.com) in two groups: active (AG, IMT with load) and SHAM (SG, placebo IMT without load). Groups will be coded, and allocation will be included in sealed and opaque envelopes numbered consecutively.

This study will include three investigators: the first will be responsible for assessments; the second, adjustment of training load; and the third, randomization. This is a double-blinded study because the first researcher and patients will be blinded to allocation of patients and intervention effects.

This protocol was approved by the research ethics committee of Universidade Federal do Rio Grande do Norte (Brazil) (CAAE**:** 45575421.7.0000.5537) on May 1, 2021 and submitted to Clinical Trials (NCT05077241). Autonomy and anonymity of patients will be respected, ensuring personal data privacy according to resolution nº 510/16 of the National Health Council and Declaration of Helsinki. Before entering the study, all patients will sign the informed consent form.

Our study was written in accordance with Standard Protocol Items: Recommendations for Interventional Trials (SPIRIT), which was aim to improve the quality of clinical trial (S1 Checklist).

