### Statistical analysis

SPSS software version 22.0 (IBM Corp. USA) will be used for data analysis. Normality will be verified using Shapiro-Wilk or Kolmogorov-Smirnov, according to the number of patients included. Variables presenting nonparametric distribution will be compared using Wilcoxon (intragroup analysis) and Mann-Whitney test (intergroup analysis), whereas repeated measures two-way ANOVA will be performed in case of parametric distribution. Dunn’s post hoc test will be used to identify significant differences in the two-way ANOVA test.

Descriptive analyses will be conducted using mean and standard deviation or median and interquartile range (25% - 75%), according to data distribution. A significance level of 5% will be applied to minimize type I error. The power of the study and effect size will also be performed for the main results of the study.

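### The power calculation planned for the main results, read as post-hoc power, only re-expresses the p-value and should be dropped or tied to a prespecified effect

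*Protocol article*

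**What the plan says.** The protocol article refers to power in two places.

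- **Type of study and location of research.** The sample size is to be computed for maximal inspiratory pressure (MIP) after a pilot of five patients per group. On the effect: "Mean and standard deviation will be used to estimate effect size". On the error rates: "a bilateral distribution with alpha error of 0.05 and 80% power will be adopted". The number is then raised for 20% dropout. This is prospective power. No numerical difference, standard deviation or sample size is given yet.
- **Statistical analysis.** After the tests and the descriptive summaries, the section sets the level ("A significance level of 5% will be applied to minimize type I error") and adds: "The power of the study and effect size will also be performed for the main results of the study".

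The second statement names no effect at which power is to be evaluated. The tests it follows are a repeated measures two-way ANOVA, or Wilcoxon and Mann-Whitney when a variable is not normally distributed. The abstract lists three primary outcomes: respiratory muscle strength, dyspnea and quality of life.

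**The concern.** Power is a property of a design at an effect chosen in advance. When the observed effect is put in its place, the result depends on the data only through the test statistic, so it carries the same information as the p-value on another scale.

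That scale misleads in one direction. A non-significant result will show low power by construction. A reader who sees this beside a null result for MIP, dyspnea or quality of life may conclude that the trial was too small to tell, when the data may in fact exclude a worthwhile effect. The reverse can also happen: a trial that really was too small gets the same figure as a large one with the same p-value. Because the trial is sized on MIP alone, from a small pilot, null results on one or more of the three primary outcomes are quite possible, and those are the results for which the figure would be consulted.

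**Working it through.** **Inputs.** Two-sided level 0.05 and design power 80% (Type of study and location of research; Statistical analysis). Two parallel arms; the allocation ratio is not stated, so 1:1 is assumed. Three assessments: before training, after training and 24 weeks (Interventions). The article gives no sample size, difference or standard deviation, so there is no figure of its own to reproduce. The per-arm sizes n below are assumptions, varied to see whether they matter.

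**Step 1: two-group normal case.** With two-sided p-value p, the observed statistic is z_obs = z(1 − p/2). Observed power = Φ(z_obs − 1.960) + Φ(−z_obs − 1.960). Neither n nor the standard deviation appears.

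- p = 0.05: z_obs = 1.960; Φ(0) = 0.500
- p = 0.10: z_obs = 1.645; Φ(−0.315) = 0.376
- p = 0.20: z_obs = 1.282; Φ(−0.678) = 0.249
- p = 0.50: z_obs = 0.674; 0.099 from the upper tail, 0.104 with both tails

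Setting the observed difference to z_obs × SD × √(2/n) and computing power directly gives the same values at n = 10, 20, 50 and 100 per arm for p = 0.05, 0.20 and 0.50 (0.500, 0.249 and 0.099, upper tail).

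**Step 2: t and F versions.** For the t test, power is taken from the noncentral t with noncentrality equal to the observed t and df = 2n − 2. For the group-by-time interaction with three time points, it is taken from the noncentral F with df1 = 2, df2 = 2(2n − 2) and noncentrality F × df1.

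| p | Normal | t, n = 5 to 50 per arm | 2-df F, n = 10 to 50 per arm |
|---|---|---|---|
| 0.01 | 0.731 | 0.739–0.835 | 0.784–0.800 |
| 0.05 | 0.500 | 0.502–0.527 | 0.583–0.584 |
| 0.20 | 0.249 | 0.234–0.248 | 0.331–0.340 |
| 0.50 | 0.104 | 0.096–0.103 | 0.160–0.166 |

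The level depends on the test and slightly on the degrees of freedom. Once these are fixed, p determines the figure. A result with p > 0.05 shows observed power below about 0.5 (normal or t) or 0.6 (2-df F).

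**Step 3: contrast with design power.** Take an assumed true difference of 0.5 SD and 63 per arm. Then 0.5 × √(63/2) = 2.806, and Φ(2.806 − 1.960) = 0.80, so the design has 80% power. If that trial ends with p = 0.20, its observed power is 0.249. The design has not changed; the 25% only repeats p = 0.20.

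**Step 4: what an interval shows and observed power hides.** Take p = 0.50 in two trials, in SD units with the SD treated as known. The estimate is 0.6745 × √(2/n) and the half-width is 1.960 × √(2/n).

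- n = 10 per arm: 0.3016 ± 0.8765, that is −0.57 to 1.18
- n = 100 per arm: 0.0954 ± 0.2772, that is −0.18 to 0.37

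Observed power is about 10% in both. The second interval excludes a difference of 0.5 SD and the first does not.

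**The case against.** The strongest reply is that the sentence never says observed or post-hoc. The sample size is open until the pilot is done and is set on MIP only, so the authors could mean power at the final sample size for the other main outcomes. That reading is possible and cannot be excluded. It is less natural: the sentence stands among the analyses of collected data, refers to the main results, pairs power with an effect size, and comes on top of a separate prospective calculation. Under either reading it needs rewording, because it does not name the effect.

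Three stronger inferences are tempting, and the document does not support them.

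- *That every significant result would appear adequately powered.* It would not. Observed power is 50% at p = 0.05 and 73% at p = 0.01 in the normal case. Reaching 80% needs z = 1.96 + 0.84 = 2.80, a p-value of about 0.005. The figure simply rises as p falls.
- *That one set of percentages applies whatever the test or sample size.* The normal-case values are free of n, the t values vary slightly, the 2-df F values are higher, and for Mann-Whitney the relation is only approximate.
- *That power is planned in place of confidence intervals.* The same sentence keeps an effect size, and the summary by "Descriptive analyses will be conducted using mean and standard deviation or median and interquartile range (25% - 75%), according to data distribution" is descriptive and excludes nothing. An article's silence on intervals is not an error when the full analysis plan may supply them.

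It is also fair to say that the document does not announce that this power will be used to explain null results. That is a foreseeable use, not a stated one.

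**Conclusion.** The point holds as a flaw of reporting and interpretation. Read in the natural way, the planned calculation tells the reader nothing beyond the p-value. It would attach a figure below about 50% (normal or t) or 60% (2-df F) to any non-significant main result, including one from a trial with 80% design power.

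This rests on the post-hoc reading, on a two-sided 5% level, and, for the numbers, on equal arms and a 2-df interaction over three time points with unadjusted degrees of freedom. The per-arm sizes are assumed but matter little.

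A reader might infer that the primary test or the type I error is compromised. Neither is affected: the calculation is an addition to the analysis and changes no test, endpoint or sample size. The effect-size half of the sentence is sound. The change should be made, but the trial's validity does not depend on it.

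**What to change.** Replace the sentence in Statistical analysis. Remove power computed from the results, keep the effect size, and state that the between-group difference will be reported with its 95% confidence interval for each main outcome (with an estimate and interval matched to the test where Mann-Whitney is used). For MIP, interpret the interval against the difference used in the final sample size calculation, once that has been set and stated; the article gives no number for it yet, and none for dyspnea or quality of life.

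If the authors meant power at the final sample size for a prespecified effect, the sentence should say so and name the effect and the outcome.

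The cost is one sentence. No data collection, test or sample size changes, and the only figure lost is one that the p-value already contains.
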